## Abstract

Supplemental Digital Content is available in the text

## Introduction

1

Neck pain is one of the most common musculoskeletal pains, with 26% to 71% of the adult population experiencing it.^[1,2]^ In particular in the Republic of Korea, non-specific chronic neck pain (CNP), diagnosed as “Back pain (M54.0)”, is the ninth among all diseases, and the second among diseases treated by Korean medicine.^[3]^ Neck pain recurs frequently, and it tends to repeat improvement and aggravation. It is likely to progress chronically, so this leads to an increase in the cost of medical services, and a decrease in the quality of life and work capacity of the worker.^[4,5]^

CNP refers to neck pain that lasts for more than 3 months without structural pathologic, or traumatic underlying causes or neurological abnormalities, such as myelopathy. CNP is classified as cervical spondylosis without myelopathy or radiculopathy (M47.8), Cervicalgia (M54.2), Myalgia, other (M79.18), based on the international classification of diseases-10 (ICD-10).^[6]^

Acupuncture is one of the treatments of complementary and alternative medicine, which is widely used in musculoskeletal pain diseases worldwide, and several clinical studies have been conducted on the acupuncture treatment of neck pain.^[7–9]^ Thread Embedding acupuncture (TEA) is an immersion method that induces continuous stimulation by embedding a thread in acupuncture points, and employs the therapeutic mechanism of delivering stimulation generated in peripheral receptors to the central nerves. It is a new acupuncture that has been widely used in recent years, and it can produce not only the stimulation effect of normal acupuncture, but also continuous effect through the buried thread. This could allow longer-term effects to be maintained with relatively few procedures.^[10]^ Recently, many clinical studies on TEA have been published in China.^[11–13]^ In the Republic of Korea, studies of Polydioxanone (PDO) TEA, which is mainly used in Korea, have been carried out. Studies that applied PDO TEA to CNP include studies on the effectiveness and safety of TEA and Sham TEA,^[14]^ and the comparison of TEA plus usual care to usual care.^[15]^

Physical therapy (PT) is widely used conservative therapy in the treatment of patients with CNP and chronic musculoskeletal pain,^[16–19]^ and in particular, heat and interfering wave therapy is commonly used PT in the Republic of Korea.^[20]^ However, no studies have compared the effectiveness and safety of PDO TEA in the treatment of patients with CNP to PT. Although a previous study compared the add-on effect of PDO TEA with the usual care,^[15]^ there was no comparison with PT only, so it was difficult to examine the exact effectiveness, safety, and long-term continuous effect of TEA compared to PT, in the treatment of patients with CNP.

Therefore, based on the assumption that PDO TEA will be more effective than PT in the treatment of patients with CNP, we have planned a large-scale, randomized, controlled, and clinical trial (RCT).

## Methods

2

### Objective

2.1

The objectives of this clinical trial are twofold: We will evaluate the effectiveness of TEA by comparing the changes in the neck pain and disability scale (NPDS) at 9 weeks (8 weeks after randomization) between the TEA group and the PT group. Adverse events (AEs) that occur during the study will be investigated to evaluate the safety of TEA.

### Study design

2.2

This clinical trial will be performed as a 2-arm parallel design, randomized, controlled, assessor-blinded, stratified block (male, female), and clinical trial. Figure 1 shows the suggested flowchart of this trial. This study is to recruit 128 applicants, who meet the criteria of inclusion and exclusion (Table 1).^[14,15,21]^ A total of 128 patients with CNP are to be recruited from Daejeon University Dunsan Korean Medicine Hospital. Applicants will be recruited through advertisements posted on bulletin boards at hospitals, subway stations, apartments, subway cars, hospital homepages, newspapers, etc. Recruitment commenced in April 2019, and the trial is expected to end in December 2019.

**Figure 1 F1:**
[figure not shown]
Study flow with outcome assessments.

**Table 1 T1:**
[figure not shown]
Inclusion and exclusion criteria.

All applicants will receive a full explanation of this trial's protocol and will be provided an informed consent form and written explanation. Also, radiography and blood tests (including liver function test, blood clotting factors, inflammation-related enzymes, etc.) will be conducted at screening visit. Participants who are judged to be eligible for this trial according to criteria will be randomly assigned in a 1:1 ratio to either the TEA group, or the PT group. The interventions will begin within 2 weeks of the screening. The subject of the TEA group will receive a total of four TEA treatments over 4 weeks, while the subject of PT group will receive a total of eight PT treatments over 4 weeks, followed by 3 follow-up visits, at 5, 9, and 13 weeks.

### Sample size calculation

2.3

Based on the results of a previous study and clinical significance,^[15,22]^ we assume that the mean difference (δ) between the changes in NPDS before and after intervention in each group is 11.5, and the standard deviation (SD, σ) is 20.67. We have applied a significance level of 5%, a power of 80%. As a result, a minimum of 51 participants are needed for each group. Also, considering the expected dropout rate of 20%, at least 64 subjects per group, for a total of 128 subjects, are required. 

### Randomization and blinding

2.4

Randomization will be conducted so as not to be biased, and be blinded to subjects and researchers. Statisticians who are not involved in the conduct and evaluation of clinical trials will randomly assign 64 patients to each group with the same probability of being selected, using the statistical program SAS Version 9.4 (SAS Institute, Inc., Cary, NC). Stratified block randomization will be used. The generated randomization table will be kept by independent statisticians and the file will be protected from disclosure.

In this trial, blinding of practitioner and subject is impossible in intervention, due to the characteristics of the procedure. However, it is designed to as much as possible be assessor-blinded to control bias. Assessments will be conducted by researchers who have not performed the intervention and randomization. The assessor will ask only simple questions about the evaluation items and the contents to fill out the case report form (CRF). The assessor does not know what kind of treatment the subject is receiving.

### Intervention

2.5

#### Thread embedding acupuncture

2.5.1

Table 2 summarizes the detailed information of TEA treatment.^[10,15,23–34]^ The patients in the TEA group will receive a total of 4 TEA treatments over 4 weeks. The TEA with a diameter of 29 gauge, and a length of 30 or 40 mm (29X36DF, 29046DF, Dongbang Medical Co., Seongnam, Republic of Korea) will be selectively used considering the depth of penetration and the muscle condition of the subject (Fig. 2). Patients are to be placed in a sitting position, with the appropriate treatment site exposed. The practitioner will insert the disposable sterile TEA, and immediately withdraws it, without further stimulation. Among the pre-selected acupuncture point pools, 4 to 8 acupuncture points will be selected per side considering the region of pain, meridian diagnosis, motion, palpation with controlled finger pressure, and spinal malalignment. The practitioner will perform a perpendicular or oblique insertion on the paravertebral point of dorsal aspect, and oblique or transverse insertion on the lateral side of the thorax and cervical vertebrae to avoid the risk of damaging critical structures, such as the external jugular vein, or common carotid artery. Before and after the treatment, Practitioners will sterilize the neck region with cotton saturated with 78% alcohol. On the day of TEA treatment, strong motion or stimulation of the treated sites will be prohibited to prevent the embedded thread from protruding. All TEA treatments will be conducted by Korean Medicine doctors (KMDs) who have had TEA treatment experience of over 3 years.

**Table 2 T2:**
[figure not shown]
TEA treatment details based on standards for reporting interventions in clinical trials of acupuncture (STRICTA) 2010 checklist.

**Figure 2 F2:**
[figure not shown]
The polydioxanone thread embedding acupuncture used in this trial.

#### Physical therapy

2.5.2

The patients in the PT group will receive a total of 8 PT treatments over 4 weeks. In patients with chronic pain, PT has been performed 2 to 3 times a week with acupuncture, whereas TEA procedures are usually applied once a week, or once every 2 weeks.^[27–33]^ Based on the results of previous clinical studies that evaluate the effect of adding TEA to usual care in the treatment of patients with non-specific CNP by using NPDS,^[15]^ we have assumed that once-a-week treatment with TEA would have an equivalent clinical effect to 2 or 3 PTs per week. Interferential current therapy (ICT) (EDiT 400, Nemectron, Karlsruhe, Germany) and heat therapy using hot pack (DS-3860H, Daeshinelc Co, Bucheon, Republic of Korea) will be applied to the PT group in this trial. With the subject in the prone position, the ICT pads will be attached to 4 points of the neck pain region, and the neuromuscular system is stimulated by crossing 2 currents (4000 or 4100 Hz) to cause interference. Depending on the subject's condition, it will be applied with an intensity of 5 to 20 mA. An electric-heated hot pack heated to 40 to 50°C will be applied to the neck.^[34]^ ICT and hot pack will be applied at the same time, and after attaching the ICT pad first, hot pack will be applied on it for about 15 minutes per session. All PT treatments will be conducted by KMDs who have had clinical experience of over 2 years. After the trial is completed, for compensation, the subjects in the PT group will receive one session of TEA treatment, upon request.

#### Cointerventions

2.5.3

All treatments for the improvement of CNP other than TEA or PT performed in this trial will be prohibited for all subjects. Medications that are considered to have no effect on this clinical trial (including other drugs for other diseases or AEs) will be allowed under the discretion of the researcher physician. Subjects will receive rescue medication (Acetaminophen 500 mg, up to 6 tablet per day), and will be instructed to take it only when their neck pain is so severe that it is unbearable. At each visit, the clinical research coordinator (CRC) will record on the CRF the total medication dosage (including rescue medication) used by the subject since the last visit. Subjects will be instructed to not take rescue medication from the day before assessments to the assessments of 5, 9, and 13 weeks. If a subject takes a drug without the report or judgment of a researcher, this can have a significant impact on the assessments of this clinical trial, so in this trial, the subject will be dropped.

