### Adverse events

2.7

In this trial, AEs are defined as all unintentional medical findings newly observed during this clinical trial. The researcher examines the AEs at each visit based on vital sign, history taking, and other examinations. Also, the subject will be instructed to voluntarily report AEs frequently, and the researcher should confirm them through medical examination. All identified AEs will be recorded on the CRF, without reference to their association with interventions. If severe AEs (SAEs) occur, the researchers will temporarily discontinue the treatment of the subject in this clinical trial. If continuous treatment is judged to be hazardous to the subject and the AE is associated with treatment, the researchers will permanently discontinue the participation of the subject in this trial.

Local discomforts after the TEA treatments could generally last about 2 days. Local discomforts that last more than 2 days after TEA treatment will be classified into AE from 2 to 7 days (delayed AE) and AE for more 7 days, and will be analyzed and reported. This is based on the previous study,^[53]^ which reported AEs from 1 to 7 days after dry needling treatment as delayed AEs, and reflects that local discomforts after TEA treatment may last longer than simple dry needling, due to the continuous stimulation by PDO.

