### Statistical analysis

2.8

All statistical analyses will be conducted as a 2-sided test, and the significance level will be set at 5%. The statistical program SAS Version 9.4 (SAS Institute Inc., Cary, NC) will be used. Multiple imputations will be used when missing values are encountered.

The data obtained from this trial will be analyzed by Full Analysis Set (FAS) and Per Protocol (PP) set. The FAS refers to the analysis method of minimizing the subjects excluded from the analysis among the randomly assigned subjects by excluding the subjects from the analysis only when there is a justifiable reason. The PP refers to the method of analyzing a group of subjects who have participated in more than 75% (3 or more TEA, 6 or more PT) of the interventions according to this clinical trial's protocol, for whom all of the assessment variables have been completely measured, and who have not violated this trial's protocol.

The descriptive statistics on the variables, such as demographic characteristics, sex, age, medical history, and drug administration will be presented for each treatment group. To verify the heterogeneity between the 2 groups at baseline, for continuous data, the mean and SD will be presented and analyzed using a Wilcoxon rank sum test or independent *t* test. The 95% confidence intervals will be provided as needed. For categorical data, frequency and percentiles will be presented and analyzed using the Fisher Exact test or Chi-square test. The primary outcome variable is the mean changes of NPDS score at 9W compared with the baseline. Analysis of covariance (ANCOVA) will be used with NPDS score at baseline as covariate and each treatment group as fixed factor. Secondary outcome variables will be analyzed in the same way as the primary outcome variables. If outcome variables are categorical variables, they will be analyzed using the Fisher Exact test or Chi-square test. The Wilcoxon signed-rank test or Paired *t* test will be used to analyze differences in measured values between pre- and post-treatment in each group. Repeated measures analysis of variance (RM-ANOVA) will be performed to examine the differences in symptom change by visit. Dunnett procedure will be used for multiple comparisons. As needed, a subgroup analysis of outcome variables such as demographic variables (age, gender, duration of illness at baseline, etc.), whether or not rescue medications were taken, and the amount of rescue medications taken can be performed.

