### Withdrawal and dropout

2.9

During the study, if the violation of inclusion or exclusion criteria of the subject is found, or if the continuous participation of subject is difficult due to the occurrence of AEs or SAEs in the subject, the subject will be dropped from this trial under the judgment of the principal investigator. The researchers will record whether each subject participating in this trial completed it or not, and if the subject is dropped, record the reasons for stopping participation in this trial.

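### The rules for dropping randomised subjects end follow-up as well as treatment, so the observed 9-week NPDS is lost for reasons that may relate to pain and to arm

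*Protocol article*

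**What the plan says.** Three sections of the protocol article remove subjects after randomisation.

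- **Cointerventions (2.5.3).** A subject who takes a drug without a researcher's report or judgment is removed. The reason given is its effect on the assessments: "this can have a significant impact on the assessments of this clinical trial, so in this trial, the subject will be dropped".
- **Adverse events (2.7).** If continued treatment is judged hazardous and the event is associated with treatment, "the researchers will permanently discontinue the participation of the subject in this trial".
- **Withdrawal and dropout (2.9).** The trigger is "if the violation of inclusion or exclusion criteria of the subject is found, or if the continuous participation of subject is difficult" because of adverse events. The consequence is that "the subject will be dropped from this trial under the judgment of the principal investigator".

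Section 2.9 also shows what dropping means: "if the subject is dropped, record the reasons for stopping participation in this trial". No section describes an assessment after that point.

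On analysis, Statistical analysis (2.8) says: "The FAS refers to the analysis method of minimizing the subjects excluded from the analysis among the randomly assigned subjects". It allows exclusion "excluding the subjects from the analysis only when there is a justifiable reason". It also plans multiple imputation for missing values, and a per-protocol set without protocol violators or subjects with incomplete assessments. The primary outcome is the change in NPDS from baseline to 9 weeks, analysed by ANCOVA with baseline NPDS as covariate.

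**The concern.** These are instructions about conduct. If they are followed as written, a subject dropped before 9 weeks never supplies the primary outcome, and no later analysis plan can recover a score that was not collected.

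The triggers are not clearly unrelated to outcome or arm. A subject who takes something outside the rules may do so because the neck still hurts. Adverse events may differ between an arm that receives embedded thread and one that receives electrical stimulation and heat. Subjects and practitioners know the treatment, and nothing says that the decision to drop is made without knowledge of the arm. If dropping depends on outcome and its frequency differs by arm, those left at 9 weeks are no longer comparable by randomisation.

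The rules also pull against the stated aim of the full analysis set (FAS). That set is meant to keep exclusions to a minimum, yet the conduct rules create avoidable missing outcomes.

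**Working it through.** **1. The plan's own figures.** Inputs from Sample size calculation (2.3): difference 11.5, SD 20.67, significance level 5% (two-sided, from 2.8), power 80%, dropout 20%.

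- n per arm = 2 × (1.960 + 0.842)² × 20.67² / 11.5² = 50.7, so 51.
- With dropout: 51 / (1 − 0.20) = 63.75, so 64 per arm and 128 in all.

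Both reproduce, so the sample size is not at fault. The allowance of 13 subjects per arm (64 − 51) protects precision. It does not protect comparability.

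**2. Does dropping end follow-up?** Section 2.7 ends participation in the trial, and 2.9 describes a dropped subject as stopping participation in the trial. Neither limits this to stopping treatment. Section 2.5.3 uses the same term. The 5-, 9- and 13-week assessments are not said to continue.

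**3. Illustration of size.** The article gives no drop rates by arm and no link between dropping and outcome, so the following are assumptions:

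- dropped fraction q of 3% in one arm against 10% in the other, or 5% against 15%;
- correlation ρ between the tendency to be dropped and the 9-week change of 0.3, 0.5 or 0.7;
- dropped subjects left out, with no imputation and no baseline adjustment.

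The shift in the mean of those retained in an arm is ρ × 20.67 × φ(z) / (1 − q), where z is the normal deviate with upper-tail area q and φ is the normal density.

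| q | z | φ(z) | φ(z)/(1 − q) |
|---|---|---|---|
| 3% | 1.881 | 0.0680 | 0.0701 |
| 5% | 1.645 | 0.1031 | 0.1086 |
| 10% | 1.282 | 0.1755 | 0.1950 |
| 15% | 1.036 | 0.2332 | 0.2743 |

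Bias in the difference between arms:

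- 3% against 10%: 20.67 × (0.1950 − 0.0701) = 2.58. Multiplied by ρ, this is 0.77, 1.29 and 1.81 points.
- 5% against 15%: 20.67 × (0.2743 − 0.1086) = 3.43. Multiplied by ρ, this is 1.03, 1.71 and 2.40 points.
- Equal rates and equal ρ: 0.

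The range of 0.8 to 2.4 points is 7% to 21% of 11.5.

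**4. Effect on the test in the same illustration.** SE = 20.67 × √(2/51) = 4.09. For biases of 1.0, 1.7 and 2.4 points, the two-sided type I error is 5.7%, 7.0% and 9.0%. If the bias acts against thread embedding acupuncture (TEA), power at 11.5 falls from 80% to 73%, 67% and 60%.

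**5. What complete follow-up would give.** With all 64 per arm assessed, SE = 20.67 × √(2/64) = 3.65 and power at 11.5 is 88%, against 80% with 51 per arm.

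**The case against.** Several stronger readings are tempting, and the text does not support them.

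- *The FAS may exclude anyone.* Section 2.8 sets out to minimise exclusions and allows them only for a justifiable reason. It gives no list of reasons and does not name the primary set, but both may stand in an analysis plan that is not shown. Neither is counted here as a fault.
- *Dropped subjects leave the primary comparison.* No section says so. Multiple imputation is planned, so a dropped subject could stay in the FAS with an imputed 9-week score. What is lost is the observed score.
- *Any adverse event leads to dropping.* The rules are narrower. Section 2.9 requires that continuing be difficult. Section 2.7 requires that it be hazardous and the event treatment-related, and a severe event first leads only to a temporary halt of treatment.
- *Imputation is useless because those retained did not need analgesia.* Rescue medication is allowed and its use is recorded, so retained subjects include some who needed it. Baseline NPDS, and the 5-week score for anyone dropped later, can inform the imputation.
- *Eight physical therapy sessions against four TEA sessions make detection unequal.* Medication is recorded as use since the last visit, so both schedules cover the same 4 weeks, and the follow-up visits are the same in both arms. The argument is weak.
- *Unreported drug use is mostly failed pain relief.* The rule covers any drug, and severe pain has a permitted outlet. The link is plausible but not shown.

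The illustration also ignores the planned imputation and ANCOVA, and the article's 20% dropout carries no difference between arms. Independent monitoring, and the preparation of the data by an independent researcher (2.10), offer some protection at the analysis stage.

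One part of the concern survives all of this. Standard multiple imputation assumes that scores are missing at random given what was observed, and that is doubtful if dropping follows pain or treatment-related events. Imputing a score that could have been collected is a poor substitute for collecting it.

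**Conclusion.** The point stands in a limited form. Sections 2.5.3, 2.7 and 2.9 end participation without providing for later assessment, so subjects dropped before 9 weeks have no observed primary outcome. The reasons for dropping can relate to pain and to arm in a trial where subjects and practitioners are unblinded. The planned imputation helps but may not fully correct this. Late-found ineligibility is the weakest trigger: it concerns entry criteria, and matters only if it is found more readily in one arm or once outcomes are known.

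The size and direction of any bias are unknown. The range of 0.8 to 2.4 points rests wholly on the assumed unequal drop rates and correlations, and on leaving dropped subjects out. A reader might take the type I error of up to 9.0% as a property of the plan. It is the upper end of that illustration and nothing more.

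**What to change.** In 2.5.3, 2.7 and 2.9, separate leaving study treatment from leaving follow-up, and leave every clinical rule on stopping treatment as it is. State that:

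- the 5-, 9- and 13-week assessments are sought in every randomised subject who has not withdrawn consent;
- unapproved drug use or late-found ineligibility is recorded as a protocol deviation and affects the per-protocol set only;
- the primary comparison includes all randomised subjects in the arm assigned, with multiple imputation for 9-week scores that are still missing.

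The cost is an amendment to the protocol wording and a few extra assessment visits for subjects who would otherwise have been dropped. No extra subjects are needed. The change helps only subjects whose assessments are still to come, so it should be made before follow-up is lost.
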